*According to the journal's guidelines, copyrighted institutional logos have been removed from the published version.*

## Additional Information on the Project

Follow-up Project of AktivDaheim, funded by FFG; Ethics Application EK No: 1505/2016

### 1. Summary

**Background:** The prevalence of dementia is increasing worldwide, leading to a growing demand for healthcare services, which is facing an increasing care gap due to the decreasing number of available caregivers. Consequently, many new technologies, such as tablet-PC training programs, have been developed with the potential to support caregivers and individuals with dementia in promoting care independence and stabilizing the course of the disease. Previous studies that include computer-based training for individuals with dementia typically focus only on the cognitive and psychological effects of primarily cognitive training programs. However, international literature recommends applying multimodal training programs (e.g., including physical and social components in addition to cognitive aspects).

**Objectives:** The primary objective is to investigate the effectiveness of the multimodal tablet-PC training program “DaheimAktiv” on cognitive abilities in individuals with early-stage Alzheimer’s dementia. Secondary objectives include assessing the usability and acceptance of the tablet, structural and functional changes in the brain, quality of life, mobility, motivation, lifestyle factors, hobbies, stress, emotions, care dependence, (instrumental) activities of daily living, medication changes, endogenous/biological factors, behavioral problems, caregiver burden, activity level, and arm strength, as well as evaluating potential depressive symptoms.

**Methods:** A mixed-method study will be conducted (1.5 years). The quantitative part is a randomized controlled trial (RCT). The qualitative part includes supplementary interviews (individual interviews, focus groups). The intervention group (110 individuals with Alzheimer’s dementia) will receive a multimodal (physical, cognitive, and social components) tablet-PC training program, while the control group (110 individuals with Alzheimer’s dementia) will receive a standard intervention. Data will be collected using tablet-PCs, eye tracking, fitness tracking, performance tests, MRI, blood samples, questionnaires, and interviews will be conducted. Additionally, supplementary questionnaires will be administered to relatives (n=220), dementia trainers (n=5), and

professional caregivers (n=5). All n=220 patients will undergo a detailed neurological and neuropsychological examination before the start of the training (=intervention group) or during the waiting period (=control group) and after the 1.5-year training/waiting interval. Furthermore, an MRI will be performed at both time points. Data analysis will be conducted quantitatively (descriptive statistics, inferential statistics) and qualitatively (content analysis).

This study promotes the development of computer-based tablet-PC training programs for the target group of Alzheimer's dementia in clinical practice.

## **2. Background**

The demographic shift is leading to an increase in older individuals with chronic conditions, such as dementia (NIH & WHO, 2011; Robert Koch Institute, 2015), and consequently an increased demand for healthcare services. However, this is countered by a growing care gap due to the decreasing number of available caregivers (Robert Koch Institute, 2015).

People in the early stages of dementia are primarily cared for at home (OECD, 2015), but as dementia progresses and care needs increase—due to care dependence (e.g., mobility, cognitive learning ability) and care issues (e.g., falls, malnutrition)—professional care becomes increasingly necessary and may end in institutional care if home care can no longer be ensured (ADI, 2013; OECD, 2015; Braunseis et al., 2012). One of the main tasks of caregiving (and primary healthcare) is to promote the independence of individuals with dementia to counteract a rapidly progressive disease course with increasing care dependence ([name], 2015). Computer-based technologies, such as tablet PC training, could support caregivers. These technologies not only have the potential to promote the (care) independence of older individuals but also to enhance their well-being (Smarr et al., 2012; WHO, 2007), which could ultimately stabilize the disease course.

So far, new technologies such as tablet PCs have been used to a limited extent in practical caregiving. The study by Nordheim et al. (2015) tested tablet PCs with individuals with

severe dementia. The use showed positive results regarding communication, motivation, and behavior of residents. The target group was individuals in nursing homes, so conclusions about people in home settings can only be drawn with limitations. The study by Lim et al. (2012) examined the usability of tablet PCs for individuals with mild dementia in a home environment and found that half of the participants were able to use the tablet independently with minimal support, despite 95% having no prior experience with tablets. The review by Joddrell et al. (2016) showed that 45 included studies demonstrated that people with dementia manage well with touchscreen technologies. International research highlights the need to include individuals with dementia in studies (Wu et al., 2014; Span et al., 2013; Mao et al., 2015) to obtain their feedback and recommendations for the further development of new technologies (Boman et al., 2014). Generally, people with dementia desire technologies that provide cognitive support, promote communication, social interaction, and life activities (e.g., mobility) (Lauriks et al., 2007; Wang et al., 2016).

Previous studies that include computer-based training for individuals with dementia using tablet PCs mostly focus solely on the cognitive and psychological effects of primarily cognitive training programs (Djabelkhir et al., 2017; Ehret et al., 2015; Fasilis et al., 2018; Garcia-Casal et al., 2017; Hitch et al., 2017; Klimova & Maresova, 2017; Nordheim et al., 2015). However, the work by Schneider & Yvon (2013) and Chalfont, Milligan, and Simpson (2018, a systematic review) suggests that interventions are more effective when conducted multimodally (i.e., also including physical and social components alongside cognitive aspects). The present study includes a multimodal PC training program for individuals with dementia, which examines effects on cognitive, psychological, physical, and ADL (activities of daily living/care dependence) levels, thereby supporting the development of computer-based training programs for the dementia target group.

### 3. Objectives

#### Primary Objective:

Examine the effectiveness of the multimodal tablet-PC training program "DaheimAktiv" on cognitive abilities in individuals with early-stage Alzheimer's dementia.

#### Secondary Objectives:

- Quantitative: Assess structural and functional changes in the brain (e.g., global and local brain volume, white matter changes), quality of life, mobility, motivation, lifestyle factors, stress, care dependence, (instrumental) activities of daily living, changes in medication, endogenous/biological factors (i.e., the significance of DNA variants, DNA methylation processes, or changes in gene expression related to dementia), behavioral problems, caregiver burden, activity level, and arm strength, as well as evaluate potential depressive symptoms and utilize the collected data for the development of a decision support system.
- Quantitative: Investigate the usability and acceptance regarding the use of the training program.
- Qualitative: Conduct supplementary interviews (focus groups and individual interviews) on usability.

### 4. Methode

#### 4.1. Design

The study is a "Mixed-Methods Study" with an "Embedded Design." The design of the quantitative part is a "Randomized Controlled Trial" (RCT). The qualitative part involves supplementary interviews (individual interviews and focus groups) with content analysis. The RCT will be registered in the database ClinicalTrials.gov

(<https://www.clinicaltrials.gov/ct2/home>). This is an exploratory study aimed at

investigating new relationships between tablet-based training and possible outcomes (e.g., cognition, motivation, quality of life).

## 4.2. Setting and Sample

### 4.2.1. Setting

The study will be conducted in Styria. Participants with dementia will come from home settings, assisted living, and nursing home environments.

### 4.2.2. Sample

The study aims to include 220 patients with Alzheimer's dementia (as per NINCDS-ADRDA criteria). Additionally, their primary relatives/informal caregivers (n=220), 5 professional caregivers and 5 M.A.S. (Alzheimer Syndrome) trainers (individuals conducting stage-specific training for people with dementia in individual and group sessions across various care settings) will be included.

[figure not shown]

Figure 1: Overview of the Randomized Controlled Trial (RCT)

#### 4.2.2.1. Inclusion and Exclusion Criteria

##### People/Person with Dementia (PwD)

###### Inclusion Criteria:

- A diagnosis of possible or probable dementia according to NINCDS-ADRDA criteria (McKhann et al., 2011).
- The person with dementia (PwD) is over 40 years old at the baseline assessment.
- The PwD speaks and understands German and possesses sufficient physical, auditory, and visual abilities to undergo a neuropsychological examination and participate in tablet-based training.
- The PwD has been receiving stable medication therapy for at least 3 months prior to the baseline visit.
- Memantine therapy must have started at least 3 months before the baseline visit.
- A relative/informal caregiver accompanies the PwD to the neurological examination at the University Clinic for Neurology at T0 and T3.
- If the PwD has paid 24-hour care, a relative must be recruited as a participant/informal caregiver.
- The PwD lives with or without a relative/informal caregiver at home (if alone, relatives/informal caregivers should live nearby).
- The PwD has professional (e.g., home nursing care) and/or informal care (e.g., by relatives) or receives no care.
- The PwD is capable of giving consent or a relative with representation authority or legal guardian provides consent to participate in the study.
- The PwD is not taking antipsychotics or antidepressants, or has been stabilized on these medications for at least 14 days before the study start.

###### Exclusion Criteria

- The PwD has participated in a clinical study in the 3 months before the baseline visit.
- The PwD is expected to be unable to complete the study.
- Any of the following signs on the brain MRI:

- ✓ Infarct near major vessels
  - ✓ More than one lacunar infarct, defined as a focal lesion in the CSF signal intensity with a diameter of less than 1.5 cm in all spatial directions.
  - ✓ A lacunar infarct in a strategically important region such as the thalamus, hippocampus in both hemispheres, or the caudate nucleus.
  - ✓ Confluent lesions of the deep white matter (Fazekas Score 3).
  - ✓ Other focal lesions that could be responsible for the patient's cognitive status (e.g., infections, space-occupying lesions, normal pressure hydrocephalus).
  - ✓ The PwD has undergone or has a planned operation with general anesthesia within the last 3 months before the baseline visit or during the study period.
- The PwD has had or is currently undergoing clinically significant immunomodulatory treatment or will receive such treatment in the future.
  - The PwD has a cancer diagnosis (last treatment  $\leq 5$  years before the baseline visit).
  - The PwD has had a myocardial infarction within the last 2 years before the baseline visit.
  - The PwD has hepatitis B, C, HIV, or syphilis.
  - The PwD has an active infectious disease.
  - The PwD suffers from a systemic disease that is likely to cause rapid deterioration or compromise safety:
    - ✓ Uncontrolled heart failure (NYHA>3)
    - ✓ BMI>40
    - ✓ Poorly controlled diabetes
    - ✓ Severe renal insufficiency
    - ✓ Chronic liver disease
    - ✓ Other clinically relevant systemic diseases.
  - The PwD suffers from hypothyroidism. Persons with treated hypothyroidism may participate if they have had stable therapy for more than 3 months before the baseline visit.

- The PwD suffers from a psychiatric illness, such as schizophrenia, psychotic disorders, or bipolar disorder.
  - ✓ The PwD currently has a depressive episode (Geriatric Depression Scale GDS  $\geq 6$  at baseline visit) or major depression within the last 2 years.
- The PwD has a metabolic or toxic encephalopathy or dementia due to general medical conditions.

### Relatives/Informal Caregivers

Inclusion Criteria:

- Adult relatives (women and men) of the participating PwD
- Live with the PwD in the same household or not
- The PwD receives or does not receive professional care
- The relative provides no care or provides care themselves
- Speaks and understands German
- Capable of giving consent

### Professional Caregivers

Inclusion Criteria:

- Adult women and men
- Qualified nurses or nursing assistants
- Speaks and understands German
- Capable of giving consent

### M.A.S. (Morbus Alzheimer Syndrom)/Dementia Trainers

Inclusion Criteria

- Adult women and men
- Trained M.A.S. trainers
- Conduct training for the participating PwD
- Speaks and understands German
- Capable of giving consent

#### **4.2.2.2. Recruitment**

Participants will be recruited through the staff of the non-profit organization Sozialverein Deutschlandsberg (SVDL) and the Austrian Red Cross (project partners) via telephone, flyers, advertisements, websites, events, social media, and personal contact. The sampling method used is "convenience sampling." Additionally, information flyers will be distributed at the SVDL and in medical practices.

#### **4.2.2.3. Randomization and Blinding**

##### Randomization of Participants with Dementia

A randomization plan will be prepared in advance. Allocation to the Intervention Group (IG) and Control Group (CG) will be determined beforehand using a random list created in Matlab. Among participants 1-110, 70% will be allocated to the IG and 30% to the CG. For participants 111-220, 30% will be allocated to the IG and 70% to the CG. This ensures that, in the case of potential enrollment difficulties, a sufficient number of participants receive the intervention. It should be explicitly noted that the aim is to provide the intervention rather than achieving equal distribution between the IG and CG. At the Department of Neurology, only the Study Nurse will know whether a patient is in the IG or CG. The investigators (neurologist, neuropsychologist) will not know the group allocation.

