##### Blinding

Blinding of the staff of SVDL and the Austrian Red Cross (ÖRK) involved in the study is not possible because the intervention is apparent.

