#### **4.6.2. Data Protection**

##### **4.6.2.1. Data Protection for Questionnaires and Interviews**

Each study participant is assigned an individual anonymized code upon inclusion or randomization, which is recorded at the University Clinic for Neurology (UK) and transmitted to the Sozialverein Deutschlandsberg (SVDL) and the Research Coordination (RK). Communication between project partners and any data transfer will occur using this code to ensure participant anonymity. Questionnaires and interviews (both individual and focus groups) are transmitted through a secure, password-protected server from the SVDL to the Medical University of Graz (MUG). All personal data of participants are handled confidentially, and interviews are anonymized during transcription. Access to data for input and analysis is limited to the University Clinic for Neurology - Clinical Department of Neurogeriatrics, the Institute for Nursing Science at MUG, and Joanneum Research Digital (research partners).

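### Quotas and a fixed switch written into the protocol allow enrolment to be steered across participant 110, and nothing places allocation after eligibility and baseline

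*Protocol*

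**What the plan says.** **Allocation.** Section 4.2.2.3 has a random list made in advance in Matlab. It states that "Among participants 1-110, 70% will be allocated to the IG and 30% to the CG" and reverses the shares for participants 111-220. The stated reason is to secure enough trained patients if enrolment proves difficult. The overall target is "The study aims to include 220 patients" (4.2.2), and the Summary gives 110 per arm ("The intervention group (110 individuals with" Alzheimer's dementia, and the same number of controls).

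**Who recruits and who is blinded.** "Participants will be recruited through the staff of the non-profit organization Sozialverein Deutschlandsberg (SVDL) and the Austrian Red Cross" (4.2.2.2), by convenience sampling. The same organisations prescreen (4.3.1) and deliver the training (Intervention Group, under 4.3.1). Under Blinding: "Blinding of the staff of SVDL and the Austrian Red Cross (ÖRK) involved in the study is not possible because the intervention is apparent". In the clinic, "At the Department of Neurology, only the Study Nurse will know whether a patient is in the IG or CG"; the neurologist and neuropsychologist do not know the arm.

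**When the arm is assigned.** No section says. The Summary places the first examination before training for the intervention group and within the waiting period for the control group. Section 4.6.2.1 says that each participant is "assigned an individual anonymized code upon inclusion or randomization", and that this code is recorded at Neurology and sent on to a partner organisation.

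**Analysis.** Section 4.5 compares the arms by ANCOVA and lists age, gender, comorbidities and education as adjustment variables. Enrolment stage is not among them.

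**The concern.** There are two separate routes to a prognostic difference between the arms before training starts.

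1. **Across the switch at 110.** A recruiter who knows that the odds of training are 70% now and 30% later has a reason to refer some patients early and others late. Under convenience sampling, the choice of whom to approach and when lies with the recruiter. If the patients referred early are milder or more motivated, the intervention group receives more of them.

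2. **Around eligibility and baseline.** If the arm exists before the T0-a and T0-b eligibility decisions and the T0 questionnaires are complete, it can influence both. One exclusion criterion is a judgement: "The PwD is expected to be unable to complete the study". Section 4.4.1 lets partner staff help patients and caregivers to complete questionnaires at home, so knowledge of the arm could also colour baseline data.

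In either case the primary comparison would count the difference as an effect of training. The listed covariates do not measure motivation or expected rate of decline.

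**Working it through.** **Step 1: reproduce the arm sizes.** Inputs are the quotas in 4.2.2.3.
- Intervention: 0.7 × 110 + 0.3 × 110 = 77 + 33 = 110.
- Control: 0.3 × 110 + 0.7 × 110 = 33 + 77 = 110.

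This matches the 110 per arm in the Summary.

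**Step 2: how much of a between-half difference reaches the comparison.** Let d be the mean prognostic difference, first half minus second half, in outcome SD units.
- Share of the intervention group from the first half: 77/110 = 0.70.
- Share of the control group from the first half: 33/110 = 0.30.
- Bias in a comparison that ignores stage: (0.70 − 0.30) × d = 0.4d.

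**Step 3: what that does to the error rate.** The documents give no SD or effect size, so d is an assumption. Take unit outcome SD, 110 per arm analysed and no covariate adjustment. Then SE = √(2/110) = 0.135, and the two-sided false-positive rate is P(|Z + bias/SE| > 1.96).

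| Assumed d (SD) | Bias 0.4d (SD) | False-positive rate |
|---|---|---|
| 0.10 | 0.04 | about 6% |
| 0.25 | 0.10 | about 11.5% |
| 0.40 | 0.16 | about 22% |

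**Step 4: what a stage term does.** If the list is concealed, each patient within a half has essentially the same chance of training whoever was referred when, so within-half comparisons are fair. Adjusting for stage uses only those comparisons and removes 0.4d. Sealing the list without a stage term does not, because the two shares in Step 2 stay at 0.70 and 0.30.

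The stage term costs precision. Its variance is (1/77 + 1/33)/2 = 0.0433/2 = 0.0216 (SE 0.147), against 2/110 = 0.0182 (SE 0.135). Relative efficiency is 0.0182/0.0216 = 0.84, so the standard error is about 9% larger. This follows from the uneven ratios, and stage-related outcome variation would offset part of it.

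**Step 5: the timing of allocation.** No arithmetic applies, so the texts are set side by side.
- Section 4.3.1 runs from prescreening to T0-a, then T0-b, then inclusion, and does not mention randomization.
- The Summary wording on the control group's waiting period can be read as the arm existing at the first examination.
- Section 4.6.2.1 offers inclusion or randomization as alternative triggers for the code and does not order them.
- Section 4.2.2.3 says who in the clinic knows the arm, but not from when, who holds the list or how an assignment is released.

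None of this proves early allocation, and none of it excludes it.

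**The case against.** **Knowledge of the quotas is inferred.** The protocol does not say that recruiters know the ratios or the running participant number. It shows that the same organisations recruit and train, not that the same individuals do. This stands as a limit. The inference is still reasonable: they are project partners, the quotas are in the protocol, and they see the arms of the patients they train.

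**There are safeguards.** Eligibility rests on examinations by blinded clinicians and a separate MRI visit, so a recruiter has limited control over a patient's number. Controls receive a licence afterwards, which weakens the motive. The planned covariates may absorb part of a prognostic shift. All of this reduces the risk, but clinic examinations cannot undo choices about whom to refer and when.

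**A reader might infer that staff can pick patient by patient because the next arm is guessable 70% of the time.** The guess rate is correct: (77 + 77)/220 = 70.0%, or about 70.6% with a running tally of past assignments. But the best guess is almost always the same arm throughout a half, so it hardly distinguishes one patient from the next. A constant 70:30 ratio would be just as guessable and would create no between-half shift. Nor is 50% the right comparator for a guesser who keeps a tally: under 1:1 allocation that guesser is right about 54% to 55.5% of the time.

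**A reader might also infer that the Study Nurse or partner staff see the next line of the list.** In that case, steering of 0.10 SD up or down by arm would give a bias of 0.20 SD and about 32% false positives, and steering of 0.20 SD would give about 84%. The protocol says only that the nurse knows a patient's arm, and that partner staff are unblinded because the training is visible. Neither statement gives access to upcoming assignments, so these rates do not describe this trial.

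**Conclusion.** The point stands in a limited form and is worth acting on before enrolment.

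- **Between-half route.** The quotas and the switch are in the protocol, the recruiting organisations are unblinded, and 40% of any first-versus-second-half difference in prognosis enters a comparison without a stage term. For assumed differences of 0.10 to 0.40 SD, the false-positive rate is about 6% to 22%. This rests on staff knowing the quotas and acting on them, on unit SD with 110 per arm, and on no help from the planned covariates. The 40% itself needs none of these assumptions and applies equally to an innocent drift in patient mix.
- **Timing route.** The protocol leaves open that the arm is known before eligibility and baseline are settled. The documents give no basis for a figure.

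The trial is not open throughout: the neurologist and neuropsychologist are blinded, which protects their ratings but not referral. A statistical analysis plan, not at hand, might add a stage term, but the order of allocation and baseline belongs in the protocol.

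**What to change.** 1. **Summary, 4.2.2.3 and 4.6.2.1.** Name a list holder from the existing team who does not recruit, train or examine. Release assignments one at a time, only after T0-a and T0-b eligibility is signed off and all T0 measures, including the home questionnaires and the MoCA, are complete. The Study Nurse and the partners learn the arm only then. Reword the Summary sentence on the control group's first examination and the code-assignment sentence to match.
2. **4.2.2.3.** Move the ratios and the switch number to a restricted document that recruiting, training and examining staff cannot see. Optionally use a pre-generated random switch point near 110 and offset the second-stage quota to keep 110:110. For example, a switch after 120 gives 84:36, then 26:74. Trainers may still sense the ratio from their caseload, so this reduces predictability without abolishing it.
3. **4.5.** Add enrolment stage, defined by the actual switch, to the ANCOVA. The first two changes do not remove the between-half route.

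**Cost.** A short amendment and a small change to the list script, with no extra patients or visits. The arm is communicated slightly later, partners cannot plan trainer capacity from the ratio, and the stage term widens the standard error by up to about 9%.

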## **4.5. Statistics**

### Quantitative Part

The data will be analyzed using IBM SPSS version 24. The significance level is set at  $\alpha = 0.05$ . Descriptive statistics will be presented as mean and standard deviation or as median and quartiles, depending on the type of distribution. Absolute and relative frequencies will be used to describe categorical data. To address the primary research question—whether tablet-based training has a positive effect on cognition—both the primary outcome (performance in the neuropsychological test battery, NTB, global score) and secondary outcome parameters (sub-tests of the NTB and other neuropsychological assessments) will be compared between the intervention group (IG) and control group (CG) using ANCOVA (adjusted for multiple comparisons). Additionally, total brain volume, the volume of brain lobes, hippocampal volume, cerebral microstructure, and functional connectivity will be measured and compared between groups. Other secondary outcome parameters will also be compared between groups using ANCOVA. Pre-post comparisons (ANOVA repeated measures) will provide insights into changes over time. Analyses will be adjusted for age, gender, comorbidities, and education level.

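### Allocation switches from 70:30 to 30:70 after participant 110, but the stated ANCOVA adjustment set omits enrolment stage, so 40% of any residual early-late difference enters the estimated training effect

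*Protocol*

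**What the plan says.** Protocol 4.2.2.3 describes a random list prepared in advance with two ratios: "Among participants 1-110, 70% will be allocated to the IG and 30% to the CG. For participants 111-220, 30" per cent go to the IG and 70% to the CG. The reason given is practical: "This ensures that, in the case of potential enrollment difficulties, a sufficient number of participants receive the intervention". The section adds that "the aim is to provide the intervention rather than achieving equal distribution between the IG and CG".

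On size, section 4.2.2 says "The study aims to include 220 patients with Alzheimer's dementia", and the Summary plans 110 patients in each arm ("The intervention group (110 individuals with" Alzheimer's dementia, and the same number of controls).

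Section 4.5 compares IG with CG by ANCOVA on the global score of the neuropsychological test battery (NTB), its sub-tests and the other secondary outcomes. It also plans group comparisons of the MRI measures and a repeated-measures ANOVA for change over time. On covariates it says: "Analyses will be adjusted for age, gender, comorbidities, and education level". Neither section 4.5 nor any other section has a term for enrolment stage, allocation block or calendar time, or a stratified comparison.

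**The concern.** When the probability of allocation changes part-way through enrolment, a patient's arm carries information about when that patient was enrolled. Randomisation then makes IG and CG comparable among participants 1-110 and, separately, among participants 111-220, but not in the pooled sample. The equal totals of 110 per arm hide this.

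Any difference between early and late enrollees that affects the outcome, and that the listed covariates do not explain, is then partly read as an effect of training. The protocol leaves room for such differences. Section 4.2.2.2 describes convenience sampling through two partner organisations and many channels. Section 4.4.1 provides for staff burden to be evaluated continuously and the protocol adjusted as needed. The primary NTB comparison, the MRI measures and all other between-group comparisons share the same exposure.

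**Working it through.** **Inputs from the protocol.** Ratios 70:30 and 30:70, switch after participant 110 (4.2.2.3); total 220 (4.2.2); 110 per arm (Summary); α = 0.05 (4.5), taken as two-sided because sidedness is not stated. The percentages are treated as exact counts.

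**Input that is assumed.** D is the early-minus-late difference in mean outcome, in SD units, left after the model covariates. The protocol gives no value. A range of 0.2 to 0.5 SD is shown.

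**1. Planned arm sizes.** IG = 0.70 × 110 + 0.30 × 110 = 77 + 33 = 110. CG = 33 + 77 = 110. This reproduces the planned 110 and 110.

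**2. Share of D that enters the contrast.** Early share of IG = 77/110 = 0.70; early share of CG = 33/110 = 0.30. Bias = (0.70 − 0.30) × D = 0.40 × D.

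**3. Type I error without a stage term.** SE = √[(1 + 0.21 D²) × 2/110], where 0.21 = 0.7 × 0.3 is the stage variance within an arm. Rejection probability = P(|Z + bias/SE| > 1.96).

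| D (SD, assumed) | Bias (SD) | Bias/SE | Type I error | Simulated |
|---|---|---|---|---|
| 0.2 | 0.08 | 0.59 | 9.1% | 9.1% |
| 0.3 | 0.12 | 0.88 | 14.3% | 14.3% |
| 0.5 | 0.20 | 1.45 | 30.4% | 28.9% |

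The simulation used 4,000 trials per value of D. With a two-level stage factor in the model, simulated bias was about zero and type I error was 4.5% to 5.2% for D from 0 to 0.8 SD. A two-level factor is enough for the design's own confounding because the ratio is constant within each stage.

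**4. Price of the stage term.** Variance without it = 2/110 = 0.01818 (SE 0.135 SD). Variance with it = 0.25 × 2 × (1/77 + 1/33) = 0.02165 (SE 0.147 SD). Ratio = 0.02165/0.01818 = 1.19, so the SE is about 9% larger (√1.19 ≈ 1.09). The design carries the information of 220/1.19 ≈ 185 evenly allocated patients.

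**5. If enrolment stops at N between 110 and 220.** IG = 77 + 0.3(N − 110), CG = 33 + 0.7(N − 110), and the factor on D is 77/IG − 33/CG.

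| N | IG / CG | Factor on D |
|---|---|---|
| 110 | 77 / 33 | 0 |
| 130 | 83 / 47 | 0.93 − 0.70 = 0.23 |
| 150 | 89 / 61 | 0.87 − 0.54 = 0.32 (unrounded 0.324) |
| 180 | 98 / 82 | 0.79 − 0.40 = 0.38 (unrounded 0.383) |
| 220 | 110 / 110 | 0.40 |

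**The case against.** The strongest reply is that D may be small and that the error rates above are an upper case. The protocol reports no drift and gives no recruitment window. Section 4.3.2.1 trains data collectors so as to limit variation between raters. The table also describes an unadjusted comparison, whereas section 4.5 plans an ANCOVA. The NTB is measured at T0-a and T3. If the baseline score were a covariate, with an assumed baseline-to-T3 correlation of 0.7 and the same D at both visits, raw differences of 0.2, 0.3 and 0.5 SD would leave 0.06, 0.09 and 0.15 SD. The SE would be about 0.096 SD and type I error about 6%, 7% and 10%. This stands as a limit on size. It does not remove the point: section 4.5 does not name the baseline score, and drift in the rate of decline would not be absorbed by it.

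A second reply is that the study is called exploratory (4.1) and that an analysis plan, not shown here, could add the term. It could. But section 4.5 goes further than leaving detail open: it names an adjustment set, and that set lacks the variable the trial's own allocation scheme calls for. The study also has a primary effectiveness objective, a primary outcome and a significance level.

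Some stronger readings are tempting, and the documents do not support them:

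- *Recruiting staff know the ratio and enrol keen families while the odds favour training.* The protocol does not say that they know it. Section 4.2.2.3 says that at Neurology only the study nurse knows allocation. The remark that partner-organisation staff cannot be blinded concerns an intervention that is visible once given. Recruiters and trainers come from the same organisations, but the text does not say that they are the same people, and eligibility is settled after the hospital examinations (4.3.1, 4.4.1).
- *Stopping early makes the bias worse.* Arm sizes become more unequal, but step 5 shows that the confounding factor shrinks, to zero at N = 110.
- *The fix worsens a precision that the protocol promises.* The protocol states no power, effect size or SD.

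**Conclusion.** The point holds. As written, the between-group comparison pools two stages with opposite allocation ratios and does not adjust for stage, so arm is confounded with enrolment stage. At full enrolment 40% of the residual early-late difference passes into the estimated effect. The bias favours the IG if early enrollees do better and the CG if late enrollees do better.

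A reader might infer that the whole early-late difference is counted as a training effect, or that the comparison is certainly biased. Neither follows. The factor is 0.40, it applies only to what the covariates leave unexplained, and the bias is zero if the stages do not differ.

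The figures of 0.08, 0.12 and 0.20 SD, with about 9%, 14% and 30% type I error, rest on the assumed D, exact 77/33 and 33/77 counts, a two-sided test and no absorption of D by other covariates. The factor of 0.40 and the imbalance behind it rest only on the stated ratios and full enrolment.

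**What to change.** In Protocol 4.5, add enrolment stage (participants 1-110 versus 111-220) as a fixed factor in the primary ANCOVA and in every other between-group model, including the MRI comparisons and the repeated-measures models. Where a repeated-measures model reads the training effect from the group-by-time term, stage should enter with its own time interaction; a stage main effect alone would not protect that term.

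The variable follows from the participant number, so no new data or change in conduct is needed. The cost is the variance factor of about 1.19 from step 4. As an illustration only, at an assumed effect of 0.378 SD, power with 220 patients falls from 80% to 73%. If the stages do not differ, that precision is given up for nothing. In return, the comparison no longer depends on assuming that they do not.
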